## Abstract

**Background:**

Thyroid cancer is the most common endocrine malignancy. Some advanced disease is, or becomes, resistant to radioactive iodine therapy (refractory disease); this holds poor prognosis of 10% 10-year overall survival. Whilst Sorafenib and Lenvatinib are now licenced for the treatment of progressive iodine refractory thyroid cancer, these treatments require continuing treatment and can be associated with significant toxicity.

Evidence from a pilot study has demonstrated feasibility of Selumetinib to allow the reintroduction of I-131 therapy; this larger, multicentre study is required to demonstrate the broader clinical impact of this approach before progression to a confirmatory trial.

**Methods:**

SEL-I-METRY is a UK, single-arm, multi-centre, two-stage phase II trial. Participants with locally advanced or metastatic differentiated thyroid cancer with at least one measureable lesion and iodine refractory disease will be recruited from eight NHS Hospitals and treated with four-weeks of oral Selumetinib and assessed for sufficient I-123 uptake (defined as any uptake in a lesion with no previous uptake or 30% or greater increase in uptake). Those with sufficient uptake will be treated with I-131 and followed for clinical outcomes. Radiation absorbed doses will be predicted from I-123 SPECT/CT and verified from scans following the therapy. Sixty patients will be recruited to assess the primary objective of whether the treatment schedule leads to increased progression-free survival compared to historical control data.

**Discussion:**

The SEL-I-METRY trial will investigate the effect of Selumetinib followed by I-131 therapy on progression-free survival in radioiodine refractory patients with differentiated thyroid cancer showing increased radioiodine uptake following initial treatment with Selumetinib. In addition, information on toxicity and dosimetry will be collected. This study presents an unprecedented opportunity to investigate the role of lesional dosimetry in molecular radiotherapy, leading to greater personalisation of therapy. To date this has been a neglected area of research. The findings of this trial will be useful to healthcare professionals and patients alike to determine whether further study of this agent is warranted. It is hoped that the development of the infrastructure to deliver a multicentre trial involving molecular radiotherapy dosimetry will lead to further trials in this field.

**Trial registration:**

SEL-I-METRY is registered under ISRCTN17468602, 02/12/2015.

**Electronic supplementary material:**

The online version of this article (10.1186/s12885-019-5541-4) contains supplementary material, which is available to authorized users.

## Background

Thyroid cancer is the most common endocrine malignancy, but remains relatively rare despite incidence doubling since the 1990s. In 2014, 3400 people in the United Kingdom (UK) were diagnosed with thyroid cancer and in 2014 approximately 370 patients died from the disease [1].

### Current treatment

A combination of surgery, radioactive iodine (RAI) therapy and long-term thyroid stimulating hormone (TSH) suppression cures many patients with differentiated thyroid cancer, namely papillary and follicular cancers. However around 10% of patients develop advanced disease which will eventually become resistant to therapy. Prognosis for these patients is poor with a 10-year overall survival rate of 10% compared with 56% in patients with RAI avid metastases [2].

### Treatment for radioiodine refractory disease

Attempts have been made in the past to restore RAI avidity with lithium carbonate [3] and retinoic acid [4], but results have been disappointing and have failed to show clear clinical benefit.

More recently a number of multi-targeted kinase inhibitors have been tested; two phase III trials have shown significant improvements in progression free survival (PFS) with Sorafenib and Lenvatinib when compared with placebo [5, 6]. While these improvements are certainly to be welcomed, both agents cause toxicities, including fatigue, diarrhoea, hand-foot syndrome, weight loss and hypertension. Since they are taken continuously to disease progression this can have a significant impact on patients’ quality of life.

### MEK and radioiodine refractory disease

Mutations of RET, RAS or BRAF are present in approximately 70% of papillary thyroid cancers [7]. These oncogenes are part of the mitogen-activated protein kinase (MAPKinase) signalling pathway. Preclinical data suggest that activation of this pathway is critical to tumour initiation and transformation, and also results in reduced expression of genes involved in iodide metabolism, in particular the sodium iodide symporter (NIS) which is responsible for the uptake of iodine by thyroid cells. For example, papillary thyroid cancers with BRAF mutations are associated with reduced expression of key genes involved in iodine metabolism, including NIS [8].

In vitro work with rat thyroid PCCL3 cells with induced BRAF mutations has shown that treating the cells with a MEK inhibitor restores expression of TSH receptors, NIS and thyroglobulin, indicating that the effects of BRAF mutation to reduce NIS expression are potentially reversible [9].

### Selumetinib

Selumetinib is an oral, potent and highly selective, allosteric MEK1/2 inhibitor. MEK1/2 are critical components of the MAPKinase pathway. This pathway is frequently dysregulated due to activating mutations in various oncogenes, including RAS or RAF. Inhibition of MEK, which lies downstream of these targets, blocks inappropriate signal transduction offering a promising therapeutic strategy. Selumetinib is not currently approved for use in any clinical indications in humans, but phase I and II trials have been conducted in pancreatic cancer [10], melanoma [11–16], non-small cell lung cancer [17–19] and differentiated thyroid cancer [20–22] and it has recently been designated orphan drug status for treatment of differentiated thyroid cancer in the United States. The drug has been found to have an acceptable side effect profile; most frequently reported side effects include diarrhoea, nausea and vomiting, dyspnoea, blurred vision, tiredness and acneiform rash.

A previously reported pilot study [21] tested the use of Selumetinib 75 mg twice daily for four weeks in patients with radioiodine refractory differentiated thyroid cancer. All participants who started therapy were able to complete the full prescribed course of Selumetinib without dose reductions or delays. No toxic effects of Grade 3 or above were noted. Of 20 participants evaluated, Selumetinib increased radioiodine uptake in 12 (60%). Eight of these 12 achieved sufficient increased uptake for further radioiodine therapy to be viable (67%). Of the eight participants treated with radioiodine, five (63%) had partial responses and three (38%) had stable disease. All participants had decreases in serum thyroglobulin level.

### Lesional dosimetry

Standard practice in the UK, endorsed by recently published guidelines [23] is to prescribe an empirical activity, typically 3.7–7.4GBq iodine-131 (I-131) to patients with metastatic disease. It is well recognised that this leads to a wide range of absorbed dose delivered to tumour targets and organs at risk, and therefore very likely to lead to widely divergent outcomes. This is in stark contrast to modern external-beam radiotherapy practice where absorbed dose delivered to target volumes and to nearby organs at risk is prescribed and can be accurately measured. There have been calls to address this issue [24]. There is evidence that the absorbed dose delivered to thyroid remnants correlates with response for patients undergoing radioiodine ablation [25] and this study will investigate a similar relationship for patients with locally advanced or metastatic disease.

The previously described pilot study [21] used pre-treatment iodine-124 (I-124) positron emission tomography (PET) to estimate absorbed dose to individual lesions. A minimum lesion absorbed dose of 20Gy was chosen as a cut off for proceeding with further I-131 therapy. The choice of cut off used in this pilot does not appear to have been made on the basis of any published data. Additionally the absorbed doses were not verified after treatment, unlike in this study.

### SEL-I-METRY trial

The SEL-I-METRY trial has been designed to demonstrate the broader clinical impact of the use of Selumetinib therapy to re-sensitise radioiodine refractory thyroid cancer patients to treatment with radioiodine. The trial will address the dosimetry of I-131 therapy to investigate the relationship between the absorbed dose delivered and the clinical benefit from therapy. In addition the extent to which the therapeutic activity of I-131 can be individualised from the absorbed doses predicted in a pre-therapy tracer study will be analysed using dosimetric calculations. It will also explore possible biomarkers for response to this strategy, including measurement of post I-131 protein bound iodine (PBI) and molecular markers both in tumour tissue and circulating cell-free DNA.

## Methods

### Design

SEL-I-METRY is a UK, single arm, multi-centre, two-stage phase II proof of concept trial investigating the use of Selumetinib to resensitise iodine refractory patients with differentiated thyroid cancer. To ensure at least 38 participants are treated with I-131, approximately 60 participants will be recruited from eight NHS Hospitals. Participants will receive 75 mg of Selumetinib orally twice daily for four weeks (dose may be reduced due to adverse events) and will then be assessed for evidence of an increase in radioiodine uptake via iodine-123 (I-123) single photon emission computed tomography/computed tomography (SPECT/CT); those showing sufficient uptake will then receive I-131 therapy (further details on patient imaging and dosimetry can be found in Additional file 1). A previous pilot study [21] used I-124 sodium iodide (NaI) although there is currently no commercially available source of this isotope in the UK. This trial therefore elected to use I-123 as an alternative to determine changes in radioiodine uptake following Selumetinib therapy, and to predict likely lesional absorbed dose in participants proceeding to I-131 therapy. The use of I-123 as opposed to I-124 is not thought to pose any significant risk to the current trial; whilst theoretically there may be advantages to using I-124, there are no known clinical comparator studies between the two techniques and a pragmatic decision to use I-123 was deemed reasonable by the trial team. An early stopping rule is incorporated in the case where none of the first 10 patients treated with Selumetinib show sufficient iodine uptake to progress to I-131 therapy; should this happen the trial may be discontinued. The study protocol and this manuscript have been written in accordance with Standard Protocol Items: Recommendations for Interventional Trials (SPIRIT) guidelines [26] (checklist included as an Additional file 2).

### Ethical approval

The trial has received ethics approval from the NHS National Research Ethics Service (NRES) East Midlands-Leicester South (15/EM/0455).

### Primary objective

This trial aims to assess the efficacy of Selumetinib followed by I-131 therapy in iodine refractory patients with differentiated thyroid cancer demonstrating increased iodine uptake following initial treatment with Selumetinib. The primary objective is to assess whether the treatment schedule leads to increased PFS compared to historical control data. PFS has been chosen as the primary endpoint assessing efficacy to allow for proof of concept in this Phase II trial to be obtained in a quick and robust manner and as it is clinically relevant to patients.

### Secondary objectives

Assess the safety and toxicity of Selumetinib;Assess efficacy based on response and overall survival of Selumetinib followed by I-131 therapy;Determine the rate of iodine uptake in metastatic lesions in iodine refractory patients with differentiated thyroid cancer treated with Selumetinib.

### Exploratory objectives

Investigate the role of lesional dosimetry using I-123 SPECT/CT to predict response to I-131 therapy;Assess correlation between PBI with absorbed doses delivered and treatment outcome in patients who receive I-131;Summarise BRAF, NRAS and TERT gene mutational status, and additional mutational analysis of relevant genes, from tissue and circulating cell-free DNA;Assess patient reported quality of life.

### Sample size

Based on previous data, median progression free survival is estimated to be approximately six months, corresponding to 25% of patients alive and progression free at 12 months [5]; a clinically important increase suggesting further investigation of Selumetinib (assuming exponential survival) is deemed to be an increase to 44% (hazard ratio = 0.6). Using a 1-sided 10% significance level, and with 80% power, 38 patients with sufficient radioiodine uptake following Selumetinib therapy are required (allowing for 10% drop out), based on a Case and Morgan two-stage design [27]. Assuming sufficient increase in iodine uptake to warrant I-131 therapy in 60% of patients [21], approximately 60 patients will be recruited in total.

A formal interim analysis will be performed after 21 participants with sufficient iodine uptake following Selumetinib treatment have been recruited and after a minimum of 12 months recruitment. If there is evidence to suggest that 12 month progression free survival is no better than 25% based upon the Nelson-Aalen estimator then the trial may be terminated early for lack of activity.

If none of the first 10 participants treated with Selumetinib has sufficient increase in iodine uptake to progress to I-131 therapy, then the trial may be discontinued. This corresponds to excluding an uptake rate of at least 26% with 95% confidence.

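### Recruiting about 60 patients does not match the stated aim of ensuring at least 38 treated with I-131: the assumed 60% uptake rate gives 36 expected, and the pilot's 60% was the rate of any increase in uptake

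*Protocol article*

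**What the plan says.** The Sample size section sets the requirement: "38 patients with sufficient radioiodine uptake following Selumetinib therapy are required (allowing for 10% drop out"). The 38 therefore already contains the drop-out allowance. It rests on the error rates "Using a 1-sided 10% significance level, and with 80% power", on 12-month progression-free survival (PFS) of 25% against 44%, and on a two-stage design. The section then moves from 38 to a total: "Assuming sufficient increase in iodine uptake to warrant I-131 therapy in 60% of patients [21], approximately 60 patients will be recruited in total".

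The Design section gives the purpose of that total: "To ensure at least 38 participants are treated with I-131, approximately 60 participants will be recruited from eight NHS Hospitals". The Abstract (Methods) states sixty without qualification.

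The Background subsection on Selumetinib describes the pilot that is cited for the 60%. Of 20 participants evaluated, 12 (60%) had increased uptake. It continues: "Eight of these 12 achieved sufficient increased uptake for further radioiodine therapy to be viable (67"%). The Lesional dosimetry subsection says the pilot's threshold for going on to I-131 was a predicted lesion absorbed dose of 20 Gy. In this trial, sufficient uptake means clinically relevant uptake in a lesion that had none before, or a rise of at least 30% in a lesion with some baseline uptake (Treatment and assessment schedules; Secondary endpoints).

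The Analysis section restricts efficacy analyses to the IU cohort unless the analysis plan says otherwise. The Primary endpoint analysis section tests PFS in that cohort.

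**The concern.** The primary test uses only participants with sufficient uptake, so the stated power depends on how many recruits enter the IU cohort and not on how many are registered. Two statements about that yield look wrong.

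First, the total, the assumed rate and the stated purpose do not fit together, because 60% of 60 is less than 38.

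Second, the assumed rate is described as the share with enough uptake to warrant I-131 and is referenced to the pilot. In the article's own summary of the pilot, 60% is the share with any increase. The share described there in nearly the same terms as the sample-size sentence is 8 of 20.

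If recruitment stopped near 60 and uptake were below 60%, the primary test would have less than the planned 80% power while still being reported as an 80% power design.

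**Working it through.** **Inputs.** From Sample size: 38 IU participants including 10% drop-out, uptake rate 60%, one-sided 10% level, 80% power, S0 = 0.25, S1 = 0.44, interim at 21 IU participants. From Design: total about 60. From Background: pilot 12/20 and 8/20.

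**Step 1: does the 38 reproduce?** Yes, under assumptions. A large-sample two-stage Nelson-Aalen calculation with the interim at 21, an assumed futility bound of z = 0 and an assumed accrual of 8 to 15 IU participants a year gives 79.5% to 82% power with 34 evaluable, and 34/0.9 = 37.8, so 38. The article gives neither the bound nor the accrual rate, and the result depends on them: at 20 a year the same calculation gives 73.5%. The 38 is not in dispute here.

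**Step 2: does the total reproduce?** The formula is total = 38 / uptake rate. At 60%, 38/0.60 = 63.3, so 64, not 60. In reverse, 60 × 0.60 = 36. For 60 recruits to give 38 on average, uptake would have to be 38/60 = 63.3%.

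**Step 3: chance of reaching 38 if recruitment stops at exactly 60.** X is binomial(60, p), with participants independent.

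| Uptake rate p | Expected IU, 60p | P(X ≥ 38) | Recruits for an expected 38 |
|---|---|---|---|
| 60% | 36 | 35% | 64 |
| 50% | 30 | 2.6% | 76 |
| 40% | 24 | 0.02% | 95 |

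Even 64 recruits do not guarantee 38. At 60% the probability is 59%. Only a rule based on the IU count meets the word *ensure*.

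**Step 4: the pilot rates.** Any increase: 12/20 = 60% (exact 95% CI 36% to 81%). Sufficient for therapy under the 20 Gy cut-off: 8/20 = 40% (19% to 64%). The 67% in the Background is 8/12, a share of those with an increase and not of all participants evaluated.

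**Step 5: approximate power at each yield.** This is single-stage, with n = 0.9 × IU number evaluable, all followed to 12 months, and z = 1.2816. Power = Φ[(d − z√(v0/n)) / √(v1/n)], where v0 and v1 are the per-participant variances under the null and the alternative.

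- Cumulative hazard: d = 1.3863 − 0.8210 = 0.5653; v0 = 0.75/0.25 = 3; v1 = 0.56/0.44 = 1.2727.
- Log cumulative hazard: d = ln(1.3863/0.8210) = 0.5239; v0 = 3/1.3863² = 1.561; v1 = 1.2727/0.8210² = 1.888.
- Proportion: d = 0.19; v0 = 0.25 × 0.75 = 0.1875; v1 = 0.44 × 0.56 = 0.2464.

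| IU number (evaluable) | Cumulative hazard | Log cumulative hazard | Proportion |
|---|---|---|---|
| 38 (34.2) | 83% | 86% | 87% |
| 36 (32.4) | 81% | 84% | 86% |
| 30 (27.0) | 74% | 79% | 81% |
| 24 (21.6) | 64% | 73% | 75% |

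Worked case, 36 on the cumulative-hazard scale: (0.5653 − 1.2816 × √(3/32.4)) / √(1.2727/32.4) = 0.885, and Φ(0.885) = 81%.

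Going from 38 to 36 costs 1 to 2 points on every scale. The two-stage approximation of Step 1 (accrual 8 to 15 a year) agrees: 78% to 80% with 32 evaluable, against 79.5% to 82% with 34.

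**The case against.** The strongest reply has three parts.

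**The gap is rounding.** Both Design and Sample size say approximately 60, and 36 participants still give about 80% power. This stands on size: the 36-versus-38 gap is trivial for power. It does not rescue the word *ensure*, which fails about two times in three at the plan's own rate.

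**38 is the target and 60 only a projection.** Design names at least 38 treated as the aim, and the interim is timed by IU count. That reading is fair, and a reader should not infer that the article fixes a hard cap at 60. But no section says recruitment continues until 38 is reached, and the Abstract gives sixty flatly. The probabilities in Step 3 apply only if recruitment does stop at 60.

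**40% belongs to a threshold this trial does not use.** The pilot's 8/20 reflects a 20 Gy cut-off, which the article itself says does not appear to rest on published data. The present criterion is looser, so 12/20 may be the closer analogue. This also stands. A reader might infer that the trial will yield only 24 IU participants, or that its true power is 64%. The documents support neither: 40% is not a forecast under this trial's definition, how many of the pilot's 12 would meet the 30% rule cannot be found in the article, and 64% is the lowest of three approximations (64% to 75%). What remains is that the sample-size sentence does not make this argument. It presents 60% as the pilot's rate of uptake sufficient for therapy.

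**Conclusion.** The text is wrong as written, with moderate severity. The total of about 60 does not follow from 38 and 60%. It gives 36 expected and a 35% chance of 38 or more, and 64 are needed for an expected 38. That discrepancy is arithmetic and needs no outside assumption beyond binomial sampling and a stop at 60. Its direct cost in power is only 1 to 2 points.

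The mislabelled source of the 60% carries more weight, because the total is sensitive to the uptake rate: 76 recruits at 50% and 95 at 40%. The 60% may well be reasonable under this trial's looser definition. The fault is that the article attributes to the pilot a quantity which its own Background reports differently, and leaves the choice unexplained. The documents do not support a conclusion that the trial is underpowered. They support the narrower one that 80% power is secured only if recruitment runs to 38 IU participants, which no section states.

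**What to change.** 1. State in Sample size and Design that recruitment continues until 38 participants are in the IU cohort, with projected totals of about 64 at 60% uptake, 76 at 50% and 95 at 40%. Bring the Abstract's sixty into line.
2. Describe the 60% as the pilot's any-increase rate (12/20), report the 8/20 under the 20 Gy cut-off beside it, and add a sentence on why 60% is a suitable planning value for uptake as this trial defines it.
3. If about 60 is a cap for practical reasons, replace the claim to ensure at least 38 with the expected IU number and approximate power over plausible rates. On the two Nelson-Aalen scales, single-stage and after 10% drop-out, this is about 81% to 84% with 36, 74% to 79% with 30 and 64% to 73% with 24. The proportion scale raises the upper ends to 86%, 81% and 75%. The trial team should replace these with figures from its own two-stage design.

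The cost is wording and a few restated figures, with no change to the endpoint, the test or patient management. Option 1 may mean more recruits and a longer accrual period if uptake is below 60%. Option 3 may mean stating a power below 80%.

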### Eligibility criteria

Inclusion and exclusion criteria can be found in Table 1. Patients with Gilbert’s syndrome (persistent or recurrent hyperbilirubinemia that is predominantly unconjugated in the absence of evidence of haemolysis or hepatic pathology) will be eligible. Eligibility waivers will not be granted in this trial.

**Table 1 Tab1:** Eligibility criteria

*Inclusion Criteria*	
- Diagnosed with locally advanced or metastatic differentiated thyroid cancer (papillary, follicular, Hürthle cell, or poorly differentiated carcinoma) with at least one measurable lesion as measured by computed tomography (CT) or magnetic resonance imaging (MRI)	
- Participants must have iodine refractory disease defined by one or more of the following: • One or more measurable lesions that do not demonstrate iodine uptake on a previous radioiodine scan (diagnostic uptake or post therapy) OR • One or more measurable lesions that have progressed by RECIST 1.1 criteria within 12 months of I-131 therapy, despite demonstrable radioiodine avidity at the time of that treatment	
- Participants must have radiological progression by RECIST 1.1 criteria within the prior 12 months	
- Measurable disease by RECIST 1.1 criteria. Baseline scan must be completed within 4 weeks prior to the start of treatment.	
- ECOG Performance Status ≤1 and able to tolerate radioiodine therapy	
- Life expectancy of at least 12 weeks	
- Required laboratory values within 14 days of day 1 of treatment: • Adequate thyroid-stimulating hormone (TSH) suppression < 0.5 mU/L • Creatinine clearance > 50 ml/min • Absolute Neutrophil Count ≥1.5 × 109/L (1500 per mm3) • Platelets ≥100 × 109/L (100,000 per mm3) • Haemoglobin > 9.0 g/dL • Serum bilirubin ≤1.5 x upper limit of normal (ULN) • Patients with no liver metastasis must have AST or ALT ≤2.5 x ULN • Patients with liver metastasis must have AST or ALT ≤5 x ULN. If patients have AST or ALT > 3.5 x ULN and ≤ 5 x ULN they must have an ALP ≤ 6 x ULN	
- Able to give informed consent and willing to follow trial protocol.	
- Aged over 18 years or over	
- Female participants of child-bearing potential must have a negative pregnancy test within 24 h prior to starting therapy and agree to use dual methods of contraception for the duration of the trial and 6 months after completing treatment. Male participants must agree to use a barrier method of contraception for the duration of the trial and 4 months after completing treatment, if sexually active with a female of child-bearing potential.	
- Able to swallow Selumetinib/I-131 capsules whole	
*Exclusion criteria*	
- Foci of anaplastic thyroid cancer	
- Able to receive curative surgery or radiation therapy	
- Major surgery (with the exception of surgical placement for vascular access), open biopsy, or significant traumatic injury ≤30 days prior to registration	
- Previous or concurrent cancer distinct in primary site or histology from thyroid cancer within previous 5 years, except for cervical cancer in situ, treated basal cell carcinoma, or squamous cell carcinoma of the skin or superficial bladder tumour	
- Have received or are receiving an IMP or other systemic anticancer treatment within 4 weeks prior to the first dose of study treatment (6 weeks for nitrosoureas, mitomycin, and suramin), or within a period during which the IMP or anticancer treatment has not been cleared from the body (e.g. a period of 5 ‘half-lives’), whichever is the most appropriate and as judged by the investigator	
- Any unresolved toxicity ≥CTCAE Grade 2 from previous anti-cancer therapy, except for alopecia	
- Prior exposure to Tyrosine Kinase, MEK, RAS or RAF inhibitors	
- Known or suspected allergy to Selumetinib or hypersensitivity to Selumetinib or any excipient agents or history of allergic reactions attributed to compounds of similar chemical or biologic composition to Selumetinib	
- Have known or suspected brain metastases or spinal cord compression, unless the condition has been asymptomatic, has been treated with surgery and / or radiation, and has been stable without requiring corticosteroids nor anti-convulsant medications for at least 4 weeks prior to the first dose of study medication.	
- Requiring medication with high iodine content (e.g. amiodarone)	
- Participants who have had a Iodine contrast enhanced CT scan in previous 2 months	
- Ophthalmological conditions as follows: • Intra-ocular pressure > 21 mmHg, or uncontrolled glaucoma (irrespective of intra-ocular pressure) • Current or past history of retinal pigment epithelial detachment (REPD)/central serous retinopathy or retinal vein occlusion	
- Any of the following cardiac conditions • Uncontrolled hypertension (BP ≥150/95 mmHg despite medical therapy) • Acute coronary syndrome within 6 months prior to starting treatment • Uncontrolled angina (Canadian Cardiovascular Society grade II-IV despite medical therapy) • Symptomatic heart failure (NYHA grade II-IV), prior or current cardiomyopathy, or severe valvular heart disease • Prior or current cardiomyopathy including but not limited to the following: • Known hypertrophic cardiomyopathy • Known arrhythmogenic right ventricular cardiomyopathy • Severe valvular heart disease • Left ventricular ejection fraction < 55% measured by echocardiography • Atrial fibrillation with a ventricular rate > 100 bpm on ECG at rest • QTcF > 450 ms or other factors that increase the risk of QT prolongation	
- Participants known to be infected with human immunodeficiency virus (HIV) or hepatitis B (HBV) or C (HCV) virus	
- Any evidence of severe or uncontrolled systemic disease (e.g. unstable or uncompensated respiratory, cardiac, hepatic, or renal disease), active infection, active bleeding (including hepatitis B, hepatitis C, HIV), diatheses or renal transplant.	
- Pregnant or breastfeeding females	
- Male or female patients of reproductive potential and, as judged by the investigator, are not employing an effective method of birth control	
- Have evidence of any other significant clinical disorder or laboratory finding that, as judged by the investigator, makes it undesirable for the patient to participate in the study.	
- Hypersensitivity to bovine or human thyroid stimulating hormone or to any of the following excipients; mannitol, sodium phosphate monobasic, monohydrate, sodium phosphate dibasic, heptahydrate or sodium chloride.	
- Hypersensitivity to I-123 or I-131 or to any of the following excipients; acetic acid, sodium hydroxide, sodium thiosulphate, sodium bicarbonate, sodium chloride, disodium phosphate anhydrous or silica	
- Patients with dysphagia, oesophageal stricture, active gastritis, gastric erosions and peptic ulcer.	
- Have refractory nausea and vomiting, chronic gastrointestinal diseases (e.g., inflammatory bowel disease), suspected reduced gastrointestinal motility or significant bowel resection that would adversely affect the absorption/bioavailability of orally administered study medication.	

